## Abstract

**Background:**

Rheumatoid arthritis is a chronic, disabling disease that can compromise mobility, daily functioning, and health-related quality of life, especially in older adolescents and young adults. In this project, we will compare a standardized Iyengar yoga program for young people with rheumatoid arthritis to a standard care wait-list control condition.

**Methods/Design:**

Seventy rheumatoid arthritis patients aged 16-35 years will be randomized into either the 6-week Iyengar yoga program (12 - 1.5 hour sessions twice weekly) or the 6-week wait-list control condition. A 20% attrition rate is anticipated. The wait-list group will receive the yoga program following completion of the first arm of the study. We will collect data quantitatively, using questionnaires and markers of disease activity, and qualitatively using semi-structured interviews. Assessments include standardized measures of general and arthritis-specific function, pain, mood, and health-related quality of life, as well as qualitative interviews, blood pressure/resting heart rate measurements, a medical exam and the assessment of pro-inflammatory cytokines. Data will be collected three times: before treatment, post-treatment, and two months following the treatment.

**Discussion:**

Results from this study will provide critical data on non-pharmacologic methods for enhancing function in rheumatoid arthritis patients. In particular, results will shed light on the feasibility and potential efficacy of a novel intervention for rheumatoid arthritis symptoms, paving the way for a larger clinical trial.

**Trial Registration:**

ClinicalTrials.gov NCT01096823

## Background

Rheumatoid arthritis (RA) is a chronic autoimmune disorder affecting over 2 million adults in the United States. Symptoms include pain, swelling, stiffness, and loss of joint function. Disability and diminished health-related quality of life (HRQOL) are commonly experienced. While RA is more typically diagnosed in older adults, many young people are also affected. Using an estimated annual prevalence of 1.3% for those under 25 years of age derived from the National Health Interview Survey, close to 400,000 children, adolescents and young adults suffer from arthritis in the U.S. [1].

The economic and personal burden of rheumatoid arthritis is high across adult and pediatric populations [2] but RA may be particularly burdensome to youth. Pain, compromised physical functioning, depression and social isolation commonly occur in affected adolescents [3,4]. Young people with arthritis or rheumatism have increased depression and pain, are more likely to use health-care services, and are less likely to attend school compared to healthy controls and also compared to adolescents with other chronic diseases [3]. An additional concern for young people with RA is the challenge to meet normative developmental milestones, such as independence. Pain and debilitated functioning may leave many in a socially and emotionally compromised state [5]. Such difficulties often persist into later adulthood. Pediatric patients with arthritis are at long-term risk of compromised physical and psychosocial functioning, including decreased rates of employment in the future [4]. Although the maintenance of physical functioning is especially important to prevent future osteoporosis and wheelchair dependency in young RA patients, the realities of mobility limitations often impedes this [6]. Clearly, young people with RA require rehabilitation efforts that target psychological and physical functioning.

Despite the need for physical and psychosocial treatments aimed at adolescents and young adults with RA, traditional approaches remain limited [6]. Current medications, including non-steroidal anti-inflammatory drugs (NSAIDs), disease-modifying rheumatic drugs (DMARDs) and steroid treatments can be useful in lessening pain and stiffness, but adverse events such as gastrointestinal problems commonly occur [7]. Such adverse side effects may compound young patients' already compromised HRQOL. Even for patients who respond well to drugs, pharmacologic therapy is often not enough. Rehabilitation efforts that promote a range of physical outcomes including ambulation, muscle strength and balance are often required to prevent joint weakness, reduced muscle efficiency, and ultimately future disability [6]. Yoga is particularly suited to meeting these rehabilitation needs, as poses designed to increase the strength and mobility of joints and muscles can be individualized to meet each patient's abilities and needs. As reviewed below, yoga has the additional advantage of addressing the patient's psychospiritual functioning, which may further reduce risk of disability.

### Yoga as treatment for chronic conditions

Yoga is a discipline developed in ancient India, characterized as a science of self-study and awareness through *asanas *(body postures), *pranayama *(patterns of breathing), and meditation. Yoga has been embraced in Western settings as a form of exercise and relaxation. Currently, yoga programs are relatively low cost, widely available and safe, when performed properly.

Only a few studies have focused on the impact of yoga on musculoskeletal conditions and none have focused specifically on young people. One study in RA patients did include adolescents but the age range was too broad (aged 15-72 years) to generalize the findings across age groups [8]. Despite the small number of participants in this study (10 in each of the yoga and control groups), yoga significantly improved handgrip strength. Handgrip strength was also significantly improved in 20 patients aged 23-43 years following yoga compared to controls [9]. Garfinkel and colleagues tested IY for 20 patients with osteoarthritis of the hands [10] and 17 patients with carpal tunnel syndrome [11]; both studies resulted in amelioration of pain and improved mobility. In 101 chronic back pain patients (aged 27-57), yoga led to improved back-related functioning, compared to an exercise control group and an education group; at 26 weeks post-intervention the yoga group further demonstrated improved pain bother and functioning compared to controls [12]. In an Iyengar yoga program for 7 patients with osteoarthritis aged 50+ years [13], significant reductions were found across functioning and pain scales. In 60 patients with chronic low back pain aged 23-67 years, Williams et al. [14] found significant improvements for an IYP compared to a control group receiving educational materials; over three quarters reported improved functionality, over half experienced reduced pain, and nearly 90% reduced pain medication.

Kuttner and colleagues [15] provided the only systematic analysis of the use of yoga for pain conditions in children and adolescents (25 IBS patients aged 11-18 years). This intervention consisted of a 4-week home practice of yoga, subsequent to an initial training session. It is unclear to what degree participants actually practiced yoga and to what extent they adhered to the prescribed yoga protocol. Despite these limitations, Kuttner et al. found that the yoga group exhibited significantly reduced IBS symptoms and disability, and improved coping and anxiety relative to wait-list controls.

### Limitations of extant research on yoga for health conditions

Among the most important limitations of the existing work on yoga are: 1) inadequate sample size; 2) overly broad age range (e.g., inclusion of adolescents and elderly patients in the same sample); 3) lack of specification regarding the tradition of yoga utilized for all but five prior studies [10-14]; 4) lack of a theoretical model to inform treatment implementation and assessment of outcomes. Since there is great variation across the numerous traditions of yoga, a lack of standardization can confound interpretations of the overall efficacy of yoga on illness states. Unlike most other studies that failed to specify the school of yogic movement utilized, we will develop an IYP with a specific set of poses that will allow reproducibility. In summary, we will address the above gaps in the literature by testing the efficacy of a standardized IYP (described below) in a well-defined population with appropriate sample size (see Power/Sample Size Calculation). Moreover, we have developed a conceptual model delineating the potential mechanisms related to the IYP to guide our proposed research.

### Biopsychosocial model of disability and pain

As a chronic condition, RA is best understood from a biopsychosocial perspective-- i.e., that psychological, biological, and social factors interact in the etiology and maintenance of RA. The biopsychosocial model has been used to understand disability, pain and treatment options for a range of chronic illnesses, including RA [16]. The conceptual model for our current study is similarly built within the biopsychosocial model [17]. It is estimated that psychosocial factors contribute up to 20% of the disability associated with RA [18,19]. Thus, an integrative treatment strategy for patients with RA is warranted. IY is a non-pharmacological rehabilitation intervention that can be combined with a conventional treatment plan. Under the conceptual model (see Figure 1), IY is viewed as impacting physical and psychospiritual well-being. Improvements in these domains in turn can lead to improvements in outcomes. The model offers a guiding heuristic for how we conceptualize the benefits of IYP for RA. We do not propose to test each pathway depicted in this preliminary study nor does the model depict all possible pathways. However, in future larger trials which will incorporate the findings of the present investigation, we plan to refine the conceptual model and test specific pathways by which yoga leads to beneficial outcomes for RA.

**Figure 1 F1:**
[figure not shown]
**Conceptual model of Iyengar yoga for RA**.

### Physiological mechanisms in yoga practice

It is thought that IY quiets the body as well as the mind through attention and relaxation [20]. Hence, yoga has been associated with a number of physical benefits including lowered autonomic arousal (including decreased diastolic and systolic blood pressure and decreased heart rate) [21-23] and a reduction in inflammatory responses in both healthy individuals [24] and those with disease [25]. A recent review concluded that yoga provides psychophysiological benefits that are particularly apparent for people with musculoskeletal conditions [26].

### Psychosocial benefits of yoga

IY has demonstrated positive effects on psychological functioning including increased self-efficacy, or the tendency to persist in health behaviors despite obstacles, and improved coping and mood. In our previous work, we [27] reported reduced depression and anxiety after a 5-week IYP. Similarly, Shapiro [28] found that a 20-week IYP led to reductions in depression, anger, anxiety, and neurotic symptoms in 17 patients (aged 20-71 years). Two other studies found significant improvements in depression, anxiety and self-efficacy following yoga [29,30]. Yoga is also associated with increased coping in patients [15,31-33]. Positive psychology, in turn, is related to better physical functioning [34]. Thus, we expect that yoga will enhance patients' coping, mood and self-efficacy, all of which will impact positively on illness-related functioning. Exercise performed in a group can also promote feelings of social well-being - important for functional status in chronic disease [35]. In future large-scale trials, we will control for such group effects, allowing us to determine the extent to which social benefits of yoga are responsible for improvements.

In contrast to established rehabilitation approaches such as exercise or physical therapy, yoga incorporates spiritual aspects that are purported to confer specific benefits including increased acceptance and mindfulness. IY leads to skill in mastering the challenges of life, which may extend to dealing with chronic illness and pain [26]. It is anticipated that the IYP will enhance patients' compassionate understanding or acceptance of one's health condition, which involves noting the pain without avoidance or limited participation in life goals [36]. Such acceptance appears to be a particularly important facet of quality of life in coping with chronic health conditions [37]. Yoga is also associated with mindful awareness, a concept that has been integrated in empirically validated approaches including cognitive-behavioral therapy [38]. Mindfulness is an openness or receptive awareness to what is occurring in the present. Mindful activity has been found to improve mood and stress [39], likely through strengthening attention on the present [20]. Use and control of attention can be turned towards minimizing stress, disability and pain. It is anticipated that IY will lead to an increase in mindfulness and acceptance which will, in turn, improve functioning among AYA with RA.

### Yoga as an innovative approach

Scientists have long recognized the health benefits of exercise for managing chronic conditions, including RA [40]. In addition to positive effects on structural and physical outcomes, exercise likely impacts brain chemistry to regulate somatomotor-sympathetic circuits and promote psychological health [41]. We propose that yoga shares many of these health benefits, in addition to psychospiritual effects that are specific to yoga practice, including mindfulness and acceptance. A further purported achievement of yoga, but not other forms of physical activity, includes control over physiological systems. Maintaining postures is thought to lead to strengthening and relaxation of voluntary muscles, and eventually to ANS control [42]. Preliminary support for this notion exists with research demonstrating voluntary control over heart rate after a 30-day yoga intervention [43]. Other benefits specific to yoga practice include a non-stressful form of physical activity that promotes an increased alignment of joints and the exploring of conscious and/or unconscious gripping or tension in the body. Such awareness can lead to the release of stress and pain in the body, as well as learning to use bodily systems more effectively. The combination of body, mind and breath awareness in yoga is thought to act on biological and psychospiritual systems to produce homeostasis across multiple aspects of an individual's functioning and physiology [26]. IY thus represents a particularly promising approach for improving RA HRQOL across multiple domains.

#### The specific aims of this research are to

**1**: Determine the feasibility of a six-week twice weekly (12 session) IYP administered in a group format to older adolescents and young adults with RA.

**2**: Compare the impact of IYP on the primary outcomes of functioning and HRQOL to that of a wait-list control group receiving usual care. Functioning will be assessed by two standardized self-report measures, one of general pain-related functioning and the other of arthritis-specific functioning.

**3**: Evaluate the effects of IYP on secondary outcomes of disease activity, pain and mood.

#### The hypotheses to be tested are

**1**: The IYP will be safe, acceptable and feasible: at least 80% of subjects will complete the IYP.

**2**: Following the IYP, participants will show significant improvement on the primary outcomes of general functioning, arthritis functioning and HRQOL relative to controls. The benefits will be apparent post-treatment and at two-month follow-up.

**3**: Following the IYP, participants will report significant improvement on the secondary outcomes of pain, DAS28, and mood compared to controls. These improvements will be evident at both post-treatment and at two-month follow-up.

## Rationale

The proposed study is innovative as it will be the first controlled investigation of a group-based, standardized IYP for older adolescents and young adults with RA. IY is a tradition of yoga that is unique in its emphasis on precise anatomical alignment, use of supportive props, and specific sequences of *asanas *(postures) (see detailed description below). An additional innovation is the use of a mixed-methods approach: patient outcomes and predictors of treatment response will be assessed using both quantitative (standardized questionnaires, physician exam, blood pressure/resting heart rate, assessment of erythrocyte sedimentation rate (ESR) and pro-inflammatory cytokines) and qualitative (interview) methods.

The selection of young patients with RA is based on key considerations. First, young people are likely to be highly motivated as RA impinges upon social, emotional and physical functioning in ways that differentiate them from their peer groups. Second, the stamina/vigor attendant with youth should enhance the ability of young people to practice IY. Third, an age group beginning at older adolescence is generally able to provide their own transportation thereby improving class attendance. Finally, in our previous work we found yoga to be very well-received by young persons [44]. Our preliminary results suggest that yoga is especially well-suited to improving HRQOL and functioning in the proposed age group.

Quality of life and functioning were chosen as the primary outcomes due to the chronic nature of RA and the recent emphasis on patient-reported outcomes in clinical research [45]. HRQOL is perhaps the most significant construct in monitoring a chronic disease's impact [46]. The increased risk of behavioral and emotional disorders faced by youth with chronic illnesses [47] underscores the need to assess and improve HRQOL, including physical, emotional and behavioral functioning. We also intend to examine biomarkers of the disease, including DAS28 scores (see Secondary Outcomes below) and pro-inflammatory cytokine responses before and after the intervention. Cytokines and their receptors likely play a role in the development and maintenance of the inflammatory process in RA [48]. Levels of interleukin-6 (IL-6) and interleukin-1 receptor antagonist (IL-1 RA) are least likely to be affected by biological agents used to treat RA and will be explored as a potential mechanism in the effect of yoga upon patient functioning.

In this study, the control condition will involve patients receiving on-going care as usual for the length of the yoga intervention. While we recognize that the control group will not account for the social aspects of the group-administered IYP, a usual care control group is necessary at this early stage of the clinical trial process. Usual care control groups are appropriate when initially testing novel interventions [49]. If the IY program is found to be superior to the wait-list group in this exploratory study, a future large-scale study will incorporate a control condition that accounts for the social, attention and expectation effects of a group-based intervention.

The overarching aim of the proposed study is to collect preliminary data on the feasibility, safety and efficacy of yoga for RA in patients aged 16-35 years to inform a larger clinical trial. Another key aim of this research is to develop a standardized yoga protocol that may be easily disseminated to other settings for future multi-center studies. The ultimate goal of this research is to begin building a strong evidence base for a readily transportable yoga treatment protocol that may be incorporated within the conventional clinical management of RA.

## Study design and methods

### Overview

This R21 project will consist of three phases: 1) treatment manual development; 2) initial administration and refinement of treatment; 3) a pilot study to evaluate treatment outcome compared to an attention wait-list control condition. These three phases are briefly summarized below.

#### Phase one (3 months)

During this phase, the initial version of the manual will be written. Based on our preliminary studies described above, this manual will describe yoga, breath and meditation exercises that are consistent with specific needs of young RA patients. Attention will also be given to how the poses can best be modified to ensure patients' joints and areas of weakness are protected. The manual will be developed by the study yoga teacher, who will review the intervention with senior Iyengar yoga teachers. During this phase, we will also develop a protocol to evaluate IY instructors' adherence to the manual.

#### Phase two (3 Months)

We will further develop the protocol by conducting an initial IY group. We will also train an additional experienced IY instructor and two assistant instructors. The two IY teachers, with their assistants, will teach a small class of 3 AYA RA patients each (total n = 6) to refine the protocol. The purpose of the assistant instructors is threefold: to promote class safety by assisting patients safely in and out of poses and to record adverse events to bring to the attention of the Safety Board (described below); to take class attendance for determination of patient adherence; and to record the poses and modifications used in each class to be evaluated by the Board (described below) for teacher adherence to the core set of poses. The assistants will note for each student: which poses were performed, which props were used, and any difficulties experienced. Weekly team meetings chaired by the PI will be conducted to solicit suggestions on additional refinements to the protocol.

#### Phase three (18 Months)

In this final phase, IY teachers will administer the IYP using the revised manual to 70 participants who will be assigned to either treatment (n = 35) or usual care control (n = 35). The controls will be immediately assigned to IYP at the end of the control phase (see Figure 2).

**Figure 2 F2:**
[figure not shown]
**Flowchart of study design**.

### Design

A randomized control trial (RCT) design will be used to examine the impact of IYP for adolescents and young adults aged 16-35 years with RA on the primary outcomes of general and arthritis-specific functioning, and the secondary outcomes of DAS28, pain and mood.

The overall design of the study is depicted in Figure 2 below. After participants have completed the telephone screening and meet the study's eligibility criteria, they will be randomized into the IYP or usual care control group. All participants will be asked to fill out consent forms before their initial medical assessment, which includes a phlebotomy, measurement of blood pressure/resting heart rate, and a joint count conducted by a physician who will be kept unaware of group assignment. Before the medical assessment, a research assistant will send a link to the questionnaires for participants who choose to complete them online. A hard copy of the questionnaires will be taken to the medical assessment if the participant chooses to complete the paper-based version in a private medical office.

Those assigned to the IYP will then engage in the 6-week program; they will repeat the baseline assessments immediately following treatment and again at a two-month follow-up. Patients initially assigned to the wait-list group will continue their usual care. Both the yoga and control groups will either receive weekly phone calls or e-mails to monitor symptoms, medication use and physical activity. After 6 weeks, control participants will be re-assessed to ensure that they still meet study eligibility criteria; those that continue to meet criteria will then take part in the IYP. Following the IYP, participants will then repeat the baseline assessments at post-treatment and two-month follow-up.

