### Exclusion criteria

Patients will be excluded from the study based on the following criteria:

• Intra-articular steroid injections within 4 weeks of screening.

• Treatment with any investigational agent within 8 weeks of screening or 5 half-lives of the investigational drug (whichever is longer).

• History of drug, alcohol, or chemical abuse within 6 months prior to screening.

• Any other disease, metabolic dysfunction, physical examination finding, or clinical laboratory finding giving reasonable suspicion that might affect the interpretation of the results or render the patient at high risk from treatment complications.

• Inability to comply with study and follow-up procedures.

• Currently pregnant.

• Previous practice of Iyengar yoga within the past three months.

• Inability to speak and understand English.

According to the Power/Sample Size calculations outlined below, we will recruit 35 patients each for the IYP and control conditions. After accounting for our projected attrition rate of 20%, we estimate there will be roughly 28 treatment completers in each condition. To accommodate 56 participants during the 36-month study period, we plan to conduct 4 initial IYP groups and 4 initial control groups, with approximately 8 patients in each group.

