### Sample Size Determination and Power Analysis

A power analysis was conducted to determine the appropriate sample size. Using a pre-test post-test for randomized groups, calculating power of the interaction of treatment by time, the sample size estimate is a total sample of 54, or 27 subjects per group (at a 0.05 significance level, 80% power for a medium effect size). We calculated a medium effect size given that our recent single-arm pilot study found an effect size of .46 (Cohen's d) for the HAQ, our arthritis-specific primary outcome measure. Assuming a 20% attrition rate that is consistent with our previous yoga studies, we will recruit 35 participants for each group (total n = 70).

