### Primary analyses

To test ***Hypothesis 2***: Participants in the IYP will demonstrate significantly greater improvement in HRQOL and functioning compared to controls. The primary outcomes include the SF-36, PDI and the HAQ. Two sets of analyses will be conducted. The first set of analyses will compare the initial yoga and control groups immediately after the IYP and control phase, respectively. Separate mixed group (yoga vs. control) by time (baseline vs. post-treatment/post-control) repeated measure analysis of variance (ANOVA) will be conducted on the primary outcomes, or the non-parametric equivalent (Friedman procedure), in the event the assumptions for parametric analyses are not met. We will use the Tukey-Fisher criteria for post hoc mean/median comparisons under the ANOVA or Friedman model. Consistent with ***Hypothesis 2***, we expect a group by time interaction wherein the yoga group will report improved functioning from baseline to post-treatment compared to the control group. The second set of analyses will assess maintenance of treatment gains during the follow-up period. If yoga and control groups do not differ significantly on SF-36, PDI and HAQ scores at baseline, then data from the two groups will be combined in order to maximize power. If groups differ at baseline, each group will be analyzed separately. Changes in SF-36, PDI and HAQ scores across baseline, post-treatment and follow-up will be evaluated using separate within-group repeated measures ANOVAs; Friedman's procedure will be used if parametric assumptions are not met. Consistent with ***Hypothesis 2***, we expect significant improvements in functioning scores from baseline to post-treatment, persisting at follow-up.

We will also conduct an ***intent-to-treat (ITT) analysis***on primary outcomes to confirm our findings in completers by including all participants who enrolled in the study, using the last observation carry forward approach. Participants who drop out will be included in the analysis by utilizing outcome scores before attrition.

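### Stopping the yoga classes is not separated from leaving the study, and the lead result rests on completers, with drop-outs' pre-attrition scores used only in a confirmatory run

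*Protocol article*

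**What the plan says.** - **Design.** Those assigned to the yoga programme take part for six weeks, and "they will repeat the baseline assessments immediately following treatment and again at a two-month follow-up". The sentence sets no condition on class attendance. Questionnaires may be completed online, and both arms are contacted weekly by phone or e-mail.
- **Hypotheses.** Hypothesis 1 is that "at least 80% of subjects will complete the IYP". Under Preliminary analyses it is examined by counting drop-outs in both arms. The Discussion says that a clearly higher drop-out rate would contradict the feasibility hypothesis.
- **Exclusion criteria, closing paragraph.** "After accounting for our projected attrition rate of 20%, we estimate there will be roughly 28 treatment completers in each condition".
- **Sample Size Determination and Power Analysis.** The same percentage inflates the sample: "Assuming a 20% attrition rate that is consistent with our previous yoga studies, we will recruit 35 participants for each group".
- **Primary analyses.** The intent-to-treat analysis is added to confirm what was found among completers, using last observation carried forward: "Participants who drop out will be included in the analysis by utilizing outcome scores before attrition".
- **Preliminary analyses.** Missing data are to be handled by multiple imputation with 20 imputations. The text does not say how this fits with the carry-forward rule.

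**The concern.** One word, attrition or drop-out, does two jobs. It measures whether people finish the yoga programme, which is a feasibility result. It also measures how many people are lost to the outcome analysis, which is a sample-size allowance. These are different events: a participant can stop attending a twice-weekly class and still answer three short questionnaires.

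The merger matters because of the analysis built on it. A comparison of completers keeps the protection of randomisation only if the people removed are similar in both arms. In the first six weeks the control arm has no classes to stop, so selection by how the yoga went can act in one arm only. The planned safeguard, comparing the baseline characteristics of completers and non-completers, cannot show how the stoppers fared at week 6. The intent-to-treat run does not resolve this as worded. The main questionnaires are given at baseline and post-treatment, so the last score of someone who drops out during the six weeks is the baseline score. A later score, even if obtained, has no place under that rule.

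**Working it through.** **1. The plan's own figures.** The plan states "the sample size estimate is a total sample of 54, or 27 subjects per group". It bases this on a 5% significance level, a power of 80% and a medium effect. A noncentral-F calculation for the group-by-time interaction with f = 0.25 and an assumed pre-post correlation of 0.2 gives 54 (power 0.81). The correlation is not stated in the article.

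Inflating for 20% attrition:
- 27 / 0.8 = 33.75, so 34 per arm (stated: 35).
- 54 / 0.8 = 67.5, so 68 in total (stated: 70).
- 35 × 0.8 = 28 per arm, the stated number of completers.

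The projected loss is 0.2 × 70 = 14 people, or 7 per arm. The 7 controls have no classes to stop in the comparison period.

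**2. Size of the possible bias.** Assumptions:
- The effect is 0.46 SD among those who finish. The pilot "found an effect size of .46 (Cohen's d) for the HAQ", but that pilot had a single arm, so using its figure as a between-group effect is only illustrative.
- 20% of the yoga arm stop.
- Controls do not change, and loss among them is unrelated to outcome.
- Stoppers change by c, in SD units.

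Formulas:
- Effect in all randomised = 0.8 × 0.46 + 0.2 × c = 0.368 + 0.2c
- Completer bias = 0.46 − (0.368 + 0.2c) = 0.092 − 0.2c
- Baseline carried forward estimates 0.8 × 0.46 = 0.368, so its bias = −0.2c

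| Stoppers' change c | Effect in all randomised | Completer bias | Carry-forward bias |
|---|---|---|---|
| 0.46 (gain fully) | 0.460 | 0 | −0.092 |
| 0.23 (gain half) | 0.414 | +0.046 | −0.046 |
| 0 (gain nothing) | 0.368 | +0.092 | 0 |
| −0.23 (worsen) | 0.322 | +0.138 | +0.046 |

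The protocol gives no value for c. The last row is a what-if only. Neither planned estimate is right across the range, and only the stoppers' own scores show which row applies.

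**3. Precision.** The standard error of a difference in means is proportional to sqrt(1/n1 + 1/n2). The reference is 28 against 28.
- Yoga arm fully retrieved (35 v 28): sqrt[(1/35 + 1/28) / (2/28)] = sqrt(0.900) = 0.949, about 5% narrower.
- Both arms fully retrieved (35 v 35): sqrt(56/70) = 0.894, about 11% narrower. This is the ceiling.

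**4. Power.** Take a medium effect as d = 0.5, two-sided, and set the SD so that 27 per arm gives 80% power: 0.5 / (2.80 × sqrt(2/27)) = 0.656. Hold that SD fixed throughout.
- 28 completers per arm, difference 0.50: 81%.
- 35 per arm, baseline carried forward for 20%, difference 0.8 × 0.50 = 0.40: 72%.
- 35 per arm with observed scores: 72% if stoppers keep none of the effect (0.40), 82% if half (0.45), 89% if all (0.50).

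**The case against.** A reader might infer that the trial stops assessing people once they stop the classes, so that the outcomes of about 20% of participants go uncollected. The document does not support that. The Design sentence refers to everyone assigned to yoga, and its words about timing set no completion condition. Nothing says that assessments end when attendance ends. A journal article may also leave off-treatment follow-up to the full protocol. So no refusal to collect data is shown.

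Other points also stand:
- Attendance is recorded separately (Phase two), and make-up classes are counted (Treatment administration).
- Because drop-outs are counted in the control arm too, the word could be read as leaving the study. On that reading the pre-attrition rule concerns people who have no later scores.
- Multiple imputation is planned, so the pre-attrition rule governs the intent-to-treat run and not necessarily every analysis.
- A modified programme for flares should keep some participants from stopping.
- The 14 projected losses cover both arms.
- The trial is exploratory.

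These points narrow the concern without removing it. The sentence on completers equates attrition with not finishing treatment, feasibility is judged by drop-outs, and the text gives the lead place to completers. Under the most generous reading of drop-out, someone who stops yoga but answers the questionnaires is still not a treatment completer and is not clearly placed in either analysis. Imputation is also no substitute for a score that can be obtained.

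**Conclusion.** The concern holds in a limited form. The fault is a completer-led primary analysis plus a pre-attrition rule in the confirmatory run, both resting on wording that does not tell stopping yoga from leaving assessment. With 20% of the yoga arm stopping, 0.46 SD among completers and unchanged controls, the completer result overstates the effect by 0.09 SD (0.092 / 0.368 = 25%) if stoppers gain nothing and is unbiased if they gain fully. Carrying baseline forward is unbiased in the first case and understates by 0.09 SD in the second. These sizes depend on an effect from a single-arm pilot and on an unknown outcome among stoppers, so they show the scale of the uncertainty and do not predict the bias. The precision gain is modest: about 5% if all yoga-arm scores are retrieved, and at most about 11% if every missing score in both arms is. The plan should be changed because the remedy is cheap and alters a rule that the article itself states.

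**What to change.** 1. **Design.** State that every randomised participant is asked for the SF-36, PDI and HAQ at week 6 and at two months, online, by e-mail or by phone, whatever their class attendance, unless they withdraw from data collection.
2. **Hypothesis 1 and sample size.** Record two separate events. Stopping the classes feeds Hypothesis 1. A missing outcome score is the attrition that the sample size allows for.
3. **Primary analyses.** Make the comparison of all participants as randomised, using scores observed at the scheduled time, the lead analysis. Remove the pre-attrition rule. Treat only scores that are truly absent as missing, and handle them by the multiple imputation already described under Preliminary analyses. Keep the completer analysis as supportive.

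The cost is a change of wording and extra contacts with the few people who stop; about 7 yoga-arm participants are projected to be lost. The SF-36 is stated to take 5-10 minutes and the PDI less than 5, and weekly contact is already planned. The estimate may be less favourable than among completers. DAS28 needs a joint count and a blood sample, so it still requires a visit and is not covered by this change.
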